## Abstract

**Background:**

Maternal mental health is vital to overall well-being, particularly among expectant and postpartum Black and Latina women who experience higher stress levels and mental health challenges. Traditional healthcare systems often fail to meet these needs, underscoring the need for innovative and accessible interventions. NurtureVR, a digital maternal mental health and educational program, leverages virtual reality to offer mindfulness, relaxation, and guided imagery to support these women.

**Objectives:**

This protocol aims to evaluate whether NurtureVR, a digital therapeutic, can reduce stress levels and mental health symptoms in pregnant and postpartum Black and Latina women, improve sleep, enhance pregnancy and childbirth experiences, and increase pregnancy and postpartum health literacy.

**Methods:**

The Nurturing Moms study uses a pre- and post-intervention design with a 5-week NurtureVR program. Fifty participants, 25 expectant and 25 postpartum Black and Latina women, will be recruited through clinics, community organizations, and online platforms. The study involves three phases: baseline assessments of stress, mood, self-efficacy, demographics, and health history; daily use of NurtureVR for 15 minutes during the third trimester and six weeks postpartum; and follow-up assessments at six weeks postpartum. The program includes 49 modules on labor and delivery, stress during pregnancy, nutrition, breastfeeding, hormonal changes, 3D VR representations of fetal development, pain management simulations, and mindfulness exercises for labor. Participants will report stress, anxiety, mood, and pain levels following each VR session. Additional qualitative insights will be gathered through focus groups, and an optional survey will be administered one-year post-intervention to evaluate long-term effects.

**Conclusions:**

The Nurturing Moms study seeks to create a more inclusive and equitable healthcare landscape, demonstrating that digital interventions like NurtureVR are essential for providing high-quality maternal care. By democratizing access to clinical research and healthcare, this decentralized trial promotes equity, improves the generalizability of findings, and accelerates the development of new treatments. The study’s innovative approach has the potential to improve maternal experiences of stress, sleep, and overall health outcomes for Black and Latina mothers and children, despite limitations such as sample size, language barriers, and the preliminary nature of a pilot and feasibility study.

## Introduction

Perinatal stress and other mental health challenges affecting mothers during pregnancy are associated with numerous adverse effects including preterm birth (1). These mental health issues are not limited to pregnancy and may persist or re-emerge in the postpartum period (2, 3). Maternal mental health disparities have been well documented, with expectant Black and Latina mothers at a significantly increased risk of severe maternal morbidity. Black mothers in particular have at least a 3.5 times increased likelihood of maternal death compared to white mothers (4, 5). The high maternal morbidity and mortality can be linked to systemic factors that often affect these populations both prior to and during the perinatal period, with racial/ethnic minority mothers experiencing more discrimination during pregnancy compared to their Non-Hispanic White counterparts (6). Specifically, pregnant Latina and Black women face significant bio-psychosocial barriers and challenges including inconsistent and low-quality prenatal care, lack of education about pregnancy, the birthing process, newborn care, and postpartum challenges. Additionally, Latina and Black mothers may experience limited access to mental health care, financial constraints, social isolation, and systemic discrimination within healthcare settings which can all have adverse effects on the baby and their overall well-being.

Traditional psychotherapy, which serves as the dominant therapeutic intervention, may not adequately address all the needs of these mothers due to its mentalistic and cognitive focus, time constraints, dependency on the therapist-client relationship, and high costs (7, 8). Furthermore, traditional psychotherapy approaches often fail to account for the unique biopsychosocial challenges faced by racial and ethnic minority groups, such as inconsistent prenatal care, lack of education on maternal and newborn health, limited access to quality mental health services, and experiences of systemic discrimination (9–11). As a result, stress and emotional distress among these populations are often not effectively managed. Addressing somatic mental health issues, such as stress, in these populations requires innovative approaches that go beyond traditional psychotherapy to provide more accessible, comprehensive, and culturally sensitive care. One potential, innovative pathway is the use of digital interventions, including virtual reality (VR) interventions. We will detail how the value of VR as a feasible, acceptable, and accessible intervention can potentially bridge the gaps in the unmet care needs of Black and Latina mothers.

The inconsistent and poor treatment of mental health issues among minoritized racial/ethnic groups can be largely attributed to mis- and under-diagnosis of mental health issues (12, 13). There are relatively low rates of mental health counseling for emotional distress in these groups due to stigma and access, but active psychoeducation from a trustworthy source may assist patients and healthcare providers in identifying and addressing perinatal emotional distress to improve maternal and fetal outcomes (14). Traditional therapies for emotional distress in mothers have lacked an educational and preventive component, and the current literature that includes Latina and African-American mothers is limited. However, our team’s own research with expecting Black and Latina mothers suggests that a virtual reality (VR) based therapy can be extremely helpful to mothers from minority backgrounds, especially in the context of addressing perinatal challenges (15).

A recent systematic review of treatments for mental health conditions in the perinatal period demonstrated that psychotherapeutic interventions such as cognitive behavioral therapy and interpersonal psychotherapy were superior to control, but the data is much less concrete in the few studies applying these interventions to low-income or minority populations (16). Similarly, there is limited evidence on the use of psychotropic medications in this population, as low-income and minority patients may have less access to specialty psychiatric care (16). Furthermore, the most recent treatment recommendations for perinatal depression highlight nearly insurmountable barriers to access, including an out-of-pocket cost of $34,000 for Brexanolone and a lack of pregnancy-related data on Zuranolone, both of which have been FDA-approved for postpartum depression in the last five years (17). With inconclusive data on psychotherapy and unrealistic pharmacotherapy options for expecting mothers, it is worthwhile to consider how a novel technology such as VR can improve access to mental health treatments and address gaps in maternal mental health psychoeducation for Latina and African-American mothers.

With a portable and commercially available headset, VR immerses the user into a three-dimensional environment with unique sounds, sights, and images. VR is not only a headset, but also an experience that includes a software program providing a highly detailed 360-degree scene. Its current potential in healthcare includes applications as vast as educating surgeons (18) to restoring executive function in people who have suffered strokes (19). VR has been used in obstetrics and gynecology to reduce pain in laboring mothers (20) and in women undergoing outpatient hysteroscopy (21). VR programs have recently been developed within the community to improve education on hypertension for African Americans (22), and to improve symptoms of anxiety in minority populations (23). Finally, researchers are taking novel steps to reach historically underrepresented groups in research to include them in VR clinical trials (24). Our protocol integrating VR to improve maternal mental health in the perinatal period in the context of a decentralized clinical trial is timely.

Unlike prior studies using VR as a reaction to treat health disturbances, the protocol described in this manuscript, *Nurturing Moms*, is designed as a *preventative* measure for Latina and African-American mothers. NurtureVR, a digital maternal mental health program, developed by BehaVR, was designed to: a) guide mothers through pregnancy via education and empathy and b) help them identify and address potential mental health concerns before these become major barriers to maternal and infant health and well-being. There is minimal research using therapeutic VR for maternal mental health in a diverse group of expecting mothers. Such work is timely, as the scientific community has only recently begun to address the importance of including diverse populations in research (25, 26). This is particularly applicable to digital health research, as the United States healthcare system continues to rapidly integrate technology into patient care. Considering this, researchers and clinicians must make a conscious effort to ensure digital health tools are accessible to all populations, especially those who have been historically neglected by the healthcare system (27).

*The Nurturing Moms* protocol (NurtureVR) addresses the aforementioned gaps in the literature by exploring Latina and Black perinatal mental health and related factors. Our primary objective is to assess whether NurtureVR reduces stress levels and mental health symptoms of pregnant and postpartum Black and Latina women. Our secondary objective is to assess whether NurtureVR improves sleep, as well as pregnancy and childbirth experiences. Our tertiary objective is to examine whether NurtureVR improves pregnancy/postpartum health literacy. We hypothesize that NurtureVR’s combination of mindfulness, relaxation, and education will be protective against postpartum depression, beneficial for pregnancy and birth experiences, and increase health literacy.

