### Study procedures

#### Timeline

The Nurturing Moms study will assess the effectiveness of NurtureVR, a digital solution for maternal mental health, across four phases. In phase I, participants will be recruited from health clinics, community-based organizations, and online platforms. Interested individuals will receive a screening form link via REDCap to determine eligibility based on inclusion and exclusion criteria (described below). Eligible participants will be contacted by a study team member to review and electronically sign an informed consent form before completing a 10–20-minute baseline questionnaire on the same platform.

In Phase II, VR headsets will be shipped to participants one week after the baseline questionnaire is completed. Participants will use the NurtureVR for five weeks and will be asked to rate their level of stress, anxiety, mood, and pain level after each VR session using well-validated scales. In Phase III, participants will repeat the surveys three months after completion of the digital intervention. Additionally, two focus group sessions will be held with five participants each, focusing on Black and Latina expectant and postpartum women’s views on resilience, their NurtureVR experiences, perceptions, and recommendations for using VR for stress management. Each focus group will be conducted online to ensure accessibility, with one session scheduled before and one after the participants’ completion of the NurtureVR program. Discussions will follow a semi-structured format, encouraging open dialogue around key themes such as resilience and VR experience. For data analysis, we will employ thematic analysis, using NVivo software to organize and code responses. This approach allows for consistent identification of recurring themes, patterns, and variations in participants’ feedback, facilitating a thorough understanding of their experiences and recommendations. Coding will be iterative and conducted by multiple researchers to enhance reliability and capture diverse perspectives.

The final phase, which is optional, invites participants to repeat the surveys one year after completing NurtureVR. This comprehensive approach aims to provide a thorough evaluation of NurtureVR’s impact on maternal mental health in the short and longer term (See **Figure 1**).

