#### Participants

Participants in the *Nurturing Moms* study will be recruited through various channels: clinical/health settings, community outreach recruitment events and community organizations, Research Match, and UMiamiHealthResearch.org. Participants will undergo a screening process in which they must meet the following inclusion criteria: 18 years old or older, speaks and understands English, Black or Latina. Additionally, they must be pregnant (less than 36 weeks) or postpartum (up to 12 months after birth). Participants will be disqualified from inclusion in the study based on the following exclusion criteria: a diagnosis of psychosis, inability to speak or understand English, or being neither pregnant (>36 weeks) nor postpartum (up to 12 months). Individuals with a history of seizures, vertigo, significant vision or hearing impairment, significant motion sickness, epilepsy, or sensitivity to flashing light/motion are also excluded from participation. Injuries to the eyes, face, neck, or arms that would make the use of the hardware uncomfortable are also grounds for exclusion. The implementation of these criteria enhances internal validity, optimizing the relevance and reliability of research findings. We aim to enroll 50 participants (25 expectant and 25 postpartum).

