#### Statistical analysis plan

For the primary objective, General Linear Model procedures will be used to examine effects of Virtual Reality (VR) on stress over time among pregnant and postpartum moms. For the secondary objective, the User Experience Questionnaire and the Virtual Reality Neuroscience Questionnaire will be used to determine feasibility, usability, and acceptability of NurtureVR as an intervention. Measures of central tendency, and frequency distributions will be used for categorical data.

The main dependent measures will be continuous factors: maternal and pregnancy mental health and sleep scores (see **Table 1** for measures). Regression analysis will be used to explore whether sociodemographic factors (e.g., age, income, education), pregnancy factors (maternal experience scale) and postpartum factors (maternal experience scale and childbirth experience questionnaire) are associated with adverse mental and sleep health outcomes. In the statistical analysis, missing data will be handled using multiple imputation techniques to minimize bias and maintain the integrity of the analysis. Outliers will be identified through visual inspections of data distributions and statistical tests, and decisions about their inclusion will be based on their potential impact on the results and the underlying reasons for their occurrence. We will use sensitivity analyses to assess the robustness of findings. Adjustments for multiple comparisons will be made using the Bonferroni correction or false discovery rate (FDR) control to reduce the risk of Type I errors due to the number of outcomes being measured. Covariates such as age, parity (number of previous births), socioeconomic status, and baseline mental health status will be included in regression models to adjust for potential confounding factors and to provide a clearer understanding of the relationships between the intervention and outcomes. Only factors that show significant correlations in preliminary analysis will be entered in the final model. These data are significant as they will be used to generate effect size estimates (and sample sizes) for planned large-scale studies and to build preliminary exploratory models ascertaining factors that predict mental and sleep health outcomes among Black and Latina pregnant and postpartum women.

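### The pregnancy- and childbirth-experience part of objective 2 cannot be answered as designed: half the women gave birth before exposure, and no woman can give a before-and-after rating of an exposed birth

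*Protocol article*

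**What the plan says.** The Introduction states: "Our secondary objective is to assess whether NurtureVR improves sleep, as well as pregnancy and childbirth experiences". The Study design overview repeats this as objective 2 and calls the study a pre-post design. Neither place limits the pregnancy and childbirth part to a cohort.

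On who enters, the Participants section says "they must be pregnant (less than 36 weeks) or postpartum (up to 12 months after birth", with no lower gestational limit, and "We aim to enroll 50 participants (25 expectant and 25 postpartum".

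On timing, the Timeline section says "VR headsets will be shipped to participants one week after the baseline questionnaire is completed", then "Participants will use the NurtureVR for five weeks", and finally "participants will repeat the surveys three months after completion of the digital intervention". Two other places differ. The Abstract describes "daily use of NurtureVR for 15 minutes during the third trimester and six weeks postpartum" and puts follow-up at six weeks after birth. The NurtureVR section describes a five-week block before birth, an optional labor block and a five-week block after it.

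On measurement, Table 2 ticks the PES and the CEQ at baseline only, while the sentence beneath it says the identical survey is sent again at three months. The one-year survey is optional, and Table 2 ticks neither scale there.

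On analysis, the Statistical analysis plan section asks whether "postpartum factors (maternal experience scale and childbirth experience questionnaire) are associated with adverse mental and sleep health outcomes". The CEQ therefore appears as an explanatory factor. What that section describes for the secondary objective is usability and acceptability, measured with two user-experience questionnaires.

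**The concern.** A pre-post claim that a programme improves an experience needs three things: the experience must come after exposure begins, it must be rated after exposure, and there must be a comparable rating from before. For childbirth, the design meets the first only in expectant women, leaves the second in doubt for everyone, and cannot meet the third for anyone. For pregnancy experience, only women still pregnant after exposure could meet all three.

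At stake is a named objective, and the Introduction's hypothesis of benefit for pregnancy and birth. A reported improvement in childbirth experience could not be interpreted. A rating collected at the wrong time, or not collected, cannot be recovered in the analysis.

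**Working it through.** **1. The plan's own figure.** The Discussion gives N = 45 for a one-sample t-test with effect size 0.5, power 95% and alpha 0.05. From the noncentral t distribution with noncentrality 0.5 × √n, a one-sided test gives N = 45 (power 95.1%), which reproduces the figure; a two-sided test gives N = 54. This does not decide whether the objective is answerable. It serves as a yardstick in step 5.

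**2. Who can have an exposed birth.** 50 − 25 = 25 women at most. The other 25/50 = 50% delivered before their first session. This needs no assumption.

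**3. What each group could supply if both scales were repeated at follow-up.**

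| Group | PES before and after, in a current pregnancy | CEQ for an exposed birth | CEQ before and after |
|---|---|---|---|
| Postpartum at entry (25) | No: pregnancy over before baseline | No: birth preceded exposure | No: both ratings concern an unexposed birth |
| Expectant, delivered by the survey | No: second rating would look back | Yes, after only | No: the birth had not happened at baseline |
| Expectant, still pregnant at the survey | Yes | Not yet | No |

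The last column is empty throughout. With Table 2 as ticked, the other two columns are empty as well, because there is no second rating.

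**4. Calendar under the Methods timeline.** Let *g* be gestational age at baseline in weeks. The Timeline section gives 1 week to shipping and 5 weeks of use, and three months is about 13 weeks:

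*g* + 1 + 5 + 13 = *g* + 19.

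Gestational age at birth is not in the article; assume 37 to 40 weeks. A woman is still pregnant at the survey if *g* < 37 − 19 = 18, up to *g* < 40 − 19 = 21. One further week for delivery of the headset makes this 17 to 20.

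How many women this affects depends on the distribution of entry, which is not given. As an illustration, with uniform entry from *L* to 36 weeks and cut-off *c*, the share is (*c* − *L*)/(36 − *L*):

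- *L* = 4: 14/32 = 44% to 17/32 = 53%, or 11 to 13 of 25.
- *L* = 8: 10/28 = 36% to 13/28 = 46%, or 9 to 12 of 25.
- *L* = 12: 6/24 = 25% to 9/24 = 38%, or 6 to 9 of 25.
- *L* = 28 (third-trimester entry, taking 28 weeks as its start): none.

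So 0 to 13 of the 25 expectant women could not yet rate childbirth, depending on the assumption.

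Under the Abstract's follow-up at six weeks after birth, every expectant woman has delivered. Under the NurtureVR section, a woman using both blocks completes after birth, so her survey also falls after it. The still-pregnant group then disappears, and with it any second PES rating of a current pregnancy. The two scales need different timing.

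**5. Size of the smaller denominator.** At n = 25 and effect size 0.5, the test in step 1 has power 78% one-sided or 67% two-sided, against the 95% planned. This is an upper bound for a paired PES comparison, since not all 25 women would still be pregnant. It does not apply to the CEQ, which has no pair.

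**The case against.** The strongest reply is that this is one part of a secondary objective in an exploratory pilot, whose Discussion already concedes that change cannot be attributed firmly without controls. Objective 1 names pregnant and postpartum women but objective 2 does not, so objective 2 can be read as concerning only women for whom it makes sense. Cohort denominators are often settled in an analysis plan that is not shown. The sentence under Table 2 implies that both scales are repeated.

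Some of this stands. The stress and sleep outcomes are untouched, and a repeated survey would give post-exposure CEQ ratings in expectant women who have delivered and paired PES ratings in those still pregnant. Adding the missing ticks is therefore necessary and useful. It would not, however, give any woman a baseline for an exposed birth or make the postpartum cohort's births exposed. Nor is this only detail left for later: the printed analysis section gives the CEQ a different role and describes a different secondary objective. A repeated CEQ in postpartum women could at most show changed recall, which the article does not state as an aim.

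Three stronger readings are tempting and not supported:

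- A reader might infer that most of the sample cannot inform this aim. Only half is certain; anything above that needs an assumed entry distribution and the Methods timeline.
- A reader might infer that early enrollees are lost altogether. They lose the childbirth rating at that survey, but they are the women who could rate pregnancy before and after exposure.
- A reader might infer that a diluted, pooled CEQ or PES score will be reported. No section plans one.

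**Conclusion.** The point holds for the pregnancy- and childbirth-experience part of objective 2. Three findings need no assumption: 25 of 50 women cannot inform it; Table 2 as printed provides no post-exposure rating in any woman and conflicts with the text beneath it; and no woman can have a pre-post change in the rating of an exposed birth. The analysis section compounds this by treating the CEQ only as a predictor.

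The 18-to-21-week cut-off is conditional on follow-up three months after a five-week programme, entry with no lower gestational limit, and birth at 37 to 40 weeks. The number of women affected is unknown, and under the timeline in the Abstract or in the NurtureVR section the problem may not arise. That conflict must itself be resolved.

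**What to change.** - Restrict the pregnancy and childbirth part of objective 2 to the expectant cohort (at most 25 women), and use the postpartum women's PES and CEQ as background only.
- Schedule the expectant cohort's CEQ from the date of birth, and add a post-exposure PES for women still pregnant at that point. Amend Table 2 and the sentence beneath it to match.
- Replace the claim that childbirth experience *improves* with a descriptive CEQ summary in women who used the programme before birth.
- Name CEQ and PES as outcomes of objective 2 in the Statistical analysis plan section.
- Reconcile the Abstract, Timeline, Participants, Table 2 and NurtureVR sections on entry window, programme span, follow-up timing and survey content. Which programme schedule is right is for the sponsor to settle.

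The cost is protocol wording, a survey link tied to the birth date and one further short questionnaire for women still pregnant. No extra participants are needed. The downside is that the denominator for this part falls from 50 to at most 25, with the loss of precision shown above.
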